**1.0 Introduction**

Carcinoma of the esophagus is an aggressive malignancy that continues to kill more than 90% of people with the disease within five years (1). The incidence of adenocarcinoma of the esophagus is rising faster than any other malignancy (2). Its virulence, in terms of symptoms and mortality, justifies a continued search for optimal therapy.

Any treatment modality chosen for esophageal cancer appears to depend on local practices. The available therapeutic options are surgery, chemotherapy, radiotherapy, and various combinations of these modalities. Recent advances in the multi-modality approach have brought about improved outcomes, but five-year survival rates remain less than 20% (3). Reasons for this poor survival include the advanced state of the disease before symptoms occur, frequent lymph node involvement (occurring in up to 60% of presenting patients), and the common occurrence of submucosal spread and extension to surrounding structures. In addition, there is no satisfactory routinely accepted method of preoperatively staging esophageal cancer.

The most recent practice guideline from Cancer Care Ontario states: “Based on the majority of the evidence available at this time, the Gastrointestinal Cancer Disease Site Group believes that preoperative chemoradiotherapy for resectable carcinoma of the esophagus is the preferred approach (4). The key evidence is drawn from a literature meta-analysis of 10 randomized trials comparing preoperative chemoradiotherapy followed by surgery to surgery alone showed a 13% absolute benefit in survival at 2 years for preoperative chemoradiotherapy (HR= 0.81; 95% CI 0.70-0.93; p=0.002) (5). A published abstract of an individual patient data (IPD)-based meta-analysis of 9 randomized trials (2,102 patients) comparing preoperative chemotherapy followed by surgery to surgery alone demonstrated a 4% (from 16 to 20%) absolute overall survival advantage for chemotherapy at 5-years (HR-0.87, 95% CI 0.79-0.95, p=0.003). Based on 7 trials (1,849 patients), the HR for disease free survival (DFS) was 0.82 (95% CI 0.74-0.91, p=0.001) in favour of CT+S, representing a 5-year absolute DFS benefit of 4% (from 6 to 10%). No difference was seen in postoperative death (6.7%) (6). Randomized trials demonstrated no survival benefit for radiotherapy given alone, either preoperatively or postoperatively, compared with surgery alone. Randomized trials demonstrated no survival benefit for postoperative chemotherapy given alone compared with surgery alone. The new standard of care for esophageal cancer appears to be preoperative chemoradiation followed by surgery for patients with operable and resectable esophageal cancer (4).

No randomized trial has evaluated postoperative chemotherapy combined with radiation versus surgery alone for esophageal cancer. Recently, the intergroup study INT-0116 randomized 556 patients, following curative resection of gastric cancer, to either postoperative combined chemoradiotherapy or observation alone (7). The treatment consisted of one cycle of 5-FU (425 mg/m2/day) and leucovorin (20 mg/m2/day) in a daily x 5 regimen followed one month later by 45 Gy (1.8 Gy/day) of radiation given with 5-FU (400 mg/m2/day) and leucovorin (20 mg/m2/day) on days 1 through 4 and the last 3 days of radiation. One month after completion of radiation, two cycles of daily x5 5-FU (425 mg/m2/day and leucovorin (20 mg/m2/day) were given at monthly intervals. Most tumours were in the distal stomach; however, tumours were present in the gastroesophageal junction in approximately 20% of patients. More than two thirds of them had either T3 or T4 tumours, and 85% had nodal metastases. The median overall survival in the surgery only group was 27 months, as compared with 36 months in the chemoradiotherapy group. The hazard ratio for death was 1.35 (95% confidence interval, 1.09 to 1.66; p=0.005). Three patients (1%) died from toxic effects of the chemoradiotherapy, and grade 3 toxic effects occurred in 41% and grade toxic effects occurred in 32%. There was a 12% survival advantage at five years with combined modality treatment reached 40%. Cancer Care Ontario now recommends postoperative chemoradiation for T3-4, N1 resected gastric cancers (8).

There have been several case series that examined the role of postoperative chemoradiation for esophageal cancer (9–12). Saito and colleagues reported on 35 patients that underwent transthoracic esophagectomy with lymphadenectomy and were subsequently treated with 50 Gy or radiation and two courses of concurrent chemotherapy (cisplatin, vindesine and pepleomycin) (9). The tolerance in all patients was good and the five-year survival rate was 31%.

Our own phase II data suggested that postoperative chemoradiation may be beneficial for esophageal cancer patients (10). Thirty-eight lymph node positive (N1) patients underwent esophagectomy followed by postoperative chemotherapy (cisplatin, 5-FU, + epirubicin) and 50 Gy radiotherapy (CRT) and 28 (N1 patients) underwent surgery alone (S). Pre-operative risk factors, tumour characteristics, ECOG scores and lengths of stay were similar. Disease-free survival was similar (CRT 10.2 months vs. S 10.6 months) but the surgery alone group had more local recurrences (CRT 13% vs. S 35%). Overall Kaplan-Meier survival analysis showed a significant advantage with postoperative chemoradiation (log rank p=0.001). The median overall survival for the chemoradiation group was 47.5 months which was significantly longer than the surgery alone group (14.1 months). The three-year survival was 62% in the CRT group and 25% in the S group, and the five-year survival was 48% and 0% respectively.

Rice and colleagues from the Cleveland Clinic compared 31 patients with locoregionally advanced esophageal cancer (90% pT3, 81% pN1, and 13% pM1a) that received postoperative adjuvant chemoradiotherapy after resection to 52 patients that underwent esophagectomy alone (11). Patients received 50.4 to 59.4 Gy external beam radiation with concurrent two 4-day cycles of intravenous 5-fluorouracil (1,000 mg/m2/d) and cisplatin (20 mg/m2/d) during the first and fourth week of adjuvant therapy. Among propensity-matched patients, median, 1-year, and 4-year survivals for those receiving adjuvant therapy versus esophagectomy were 28 versus 15 months, 60% + 11% versus 65% + 11%, and 44%+11% versus 0% (P=0.05). Median time to recurrence was 25 versus 13 months (P =0.04), and recurrence-free survival was 22 versus 10 months (P=0.02). The authors concluded that patients with locoregionally advanced carcinoma after esophagectomy should be considered for adjuvant therapy.

In a more recent cohort series report, Liu et al from China compared patients with T3-4 and N0-1 esophageal cancer that underwent either post-operative concurrent chemoradiotherapy with weekly cisplatin 30 mg/m2 followed by systemic adjuvant chemotherapy (four monthly cycles of cisplatin 20 mg/m2 and 5-fluorouracil 1 000 mg/m2 for five consecutive days), or, post-operative radiation alone (12). The radiotherapy dose was 55-60 Gy for all patients. A total of 60 patients (n = 30 per group) were enrolled in this study. The two groups were generally comparable for demographic characteristics and hematological and non-hematological toxicities. The treatment with weekly cisplatin was well tolerated, with significantly better mean overall survival (30.9 months vs 20.7 months; 95% CI, 27.5-36.4 vs 15.2-26.1) and 3-year survival (70.0% vs 33.7%; P = 0.003). Low histological grade of tumor (P<0.001) was associated with favorable survival in these locally advanced patients. They concluded for locally advanced esophageal cancer, the combination of esophagectomy, post-operative chemoradiotherapy with weekly cisplatin and systemic adjuvant chemotherapy was well tolerated and effective.

Optimal radiation therapy target volume definition for esophageal cancer patients receiving primary chemoradiation therapy is controversial, partly due to significant changes in patient anatomy and function, and partly due to limited information available to evaluate the benefit on anastomotic site coverage in the post-surgical radiation therapy target volume. Our own experience (13) showed a significant reduction in local recurrence using extended volume external beam radiation therapy covering the anastomotic site in post – esophagectomy high risk patients.

There has never been a direct comparison of preoperative chemoradiation to postoperative chemoradiation for esophageal cancer. We propose to determine if there is an advantage for either preoperative chemotherapy and radiotherapy followed by surgery or surgery followed by postoperative chemotherapy and radiotherapy. The study builds upon the results of the previous intergroup trials, three phase II trials and our own experience and represents the next logical treatment option.

**2.0 Hypothesis**

Postoperative cisplatin, 5-FU, and epirubicin chemotherapy with concurrent extended volume radiotherapy following surgical resection is superior to standard preoperative cisplatin and 5-FU chemotherapy plus radiotherapy followed by surgical resection for resectable esophageal carcinoma.

**3.0 Objectives**

The main objective is to compare adjuvant cisplatin, epirubicin, and 5-FU with concurrent extended volume radiotherapy following surgical resection (adjuvant trimodality therapy) to preoperative cisplatin and 5-FU chemotherapy and surgery (induction trimodality therapy).

**3.1 Primary Objectives**

3.1.1 To compare the disease specific health-related quality-of-life using the FACT-E between the two treatments.

**3.2 Secondary Objectives**

3.2.1 To assess and compare the toxicities and morbidities of each approach.

3.2.2 To compare overall survival rates between the two treatment arms.

3.2.3 To compare recurrence in the two groups including local (gastric or esophageal bed), regional (regional lymph nodes), and distant recurrences (supraclavicular lymph node, liver, peritoneal carcinomatosis, or lung, brain, etc.).

3.2.4 To conduct an economic analysis comparing the two treatments.

3.2.5 To compare the proportion of complete (R0), microscopic positive (R1), and grossly positive (R2) resections between treatment arms.

**4.0 Primary Endpoint:**

**Health-Related Quality-of-Life**

Three health-related quality-of-life instruments will be used. They will include a utility instrument, a generic health index, and two disease-specific instruments, representing the full spectrum of different approaches to Health-Related Quality of Life (HRQOL) measurement. The primary outcome will be the FACT-E.

**4.1 The Functional Assessment of Cancer Therapy – Esophageal (FACT-E)**

The Functional Assessment of Cancer Therapy-General (FACT-G) is a self-administered 27 item general cancer quality of life (QL) measure for evaluating patients receiving cancer treatment (14,15). The FACT G meets or exceeds all requirements for use in oncology clinical trials, including ease of administration, brevity, reliability, validity, and responsiveness to clinical change (16). It is divided into four primary domains: physical well-being, social / family wellbeing, emotional wellbeing, and functional well-being.

The FACT-E has recently been developed and validated (17). It is a quality-of-life subscale for patients with esophageal cancer to be used with the FACT-G and provides a more multidimensional assessment of HRQOL than the EORTC QLQ-C30/QLQ-OG25 (18–22). It captures the clinically relevant problems associated with esophageal cancer patients and takes less than 10 minutes to administer. The FACT-G consists of 27 items divided among 4 subscales: physical well-being (PWB), functional well-being (FWB), social/family well-being (SWB), and emotional well-being (EWB). The sum of these subscales forms the total FACT-G score. The FACT-G has been well studied and previously validated (19). The Esophageal Cancer Subscale (ECS) of the FACT-E addresses concerns specific to patients with esophageal cancer such as eating, appetite, swallowing, pain, talking/communicating, mouth dryness, breathing difficulty, coughing, and weight loss. The total FACT-E score is the sum of the ECS and the FACT-G scores. A trial outcome index (TOI) score, useful where the physical domains are of interest, is computed by adding the PWB and FWB scores to the ECS score. All FACT-E items are rated on a 5-point Likert scale ranging from 0 = ‘‘not at all’’ to 4 = ‘‘very much’’. Negatively worded items are reverse scored so that higher scores always represent better quality of life (QOL) or less severe symptoms. Possible score ranges are PWB (0–28), FWB (0–28), SWB (0–28), EWB (0–24), ECS (0–68), TOI (0–124), swallowing index (0–20), eating index (0–12), FACT-G (0–108), and FACT-E (0–176).Yost and Eton have reviewed combining distribution- and anchor-based approaches to determine minimal clinically important difference values for the various FACT instruments by disease site and suggested a range between 5% and 10%, translating to a range of 8.8 to 17.6 points for FACT-E based on a total score of 176 points (23). The a priori minimal clinically important difference was conservatively set at 15 indicating that a 15-point increase in the FACT-E score compared to baseline would correspond with a clinically meaningful positive effect on HRQOL for the patient (24).

A prospective cohort study of patients with esophageal cancer treated with surgery alone or neoadjuvant chemoradiotherapy and surgery evaluating the validity, internal consistency, and responsiveness to change of the FACT-Esophageal (FACT-E) when comparing it with the European Organization for the Research and Treatment of Cancer Quality of Life Questionnaire (EORTC QLQ 30) and esophageal (OES 24) as well as clinical factors. The FACT-E demonstrated very good convergent and divergent validity when compared with the EORTC QLQ30 and OES 24 and clinical variables. Internal consistency was also good with coefficient alpha > 0.70 for all subscales and individual items. Stability coefficients were > 0.80. Changes in clinical status were reflected in changes in FACT-E scores demonstrating responsiveness to change, particularly in patients receiving neoadjuvant chemoradiotherapy before surgery. The FACT-E met or exceeded all standards for validity, providing an option to measure health-related quality of life for different treatment strategies for esophageal cancer. The FACT-E contains a summative domain with standard deviation and clinical effect size information that can be used for sample size calculation.

**4.2 The EORTC QLQ-OG25**

The most recent instrument is the EORTC QLQ-OG (18). It combines the EORTC questionnaires for assessing quality of life (HRQL) for esophageal (QLQ-OES18) and stomach cancer (QLQ-STO22), into a single questionnaire for tumours of the esophagus, Oesophago-gastric junction, or stomach. The QLQ-OES18, QLQ-STO22 and seven modified items were administered to 300 patients with oesophageal (n=148), junctional (n=66), or gastric cancer (n=86). Semi-structured interviews assessed item and scale preference and multi-trait scaling analyses confirmed the scale structure of the new module (QLQ-OG25). This was further tested for validity. The QLQ-OG25 has six scales, dysphagia, eating restrictions, reflux, odynophagia, pain, and anxiety. Scales have good reliability (alpha range 0.67-0.87), and they distinguish between tumour sites and disease stage. Scales do not correlate highly with scores from the core questionnaire, thus indicating that the module was addressing separate HRQL aspects. Questionnaire responses were transformed linearly into scores ranging from 0 to100 according to the EORTC scoring manual (28). A higher score indicates either more symptoms or better function, depending on the question. The minimal clinically important difference is estimated to be 10 (24). The QLQ-OG25 is recommended to supplement the EORTC QLQ-C30 when assessing HRQL in patients with esophageal, junctional, or gastric cancer. The FACT-E and EORTC QLQ-OG25 questionnaires assess similar generic aspects of quality of life. The correlation between them is poor except for the swallowing domain (19). We therefore believe that both instruments should be used.

**4.3 EuroQoL EQ-5D**

EQ-5D is a standardized instrument for use as a measure of health outcome (20). It is applicable to a wide range of health conditions and treatments; it provides a simple descriptive profile and a single index value for health status. EQ-5D was originally designed to complement other instruments but is now increasingly used as a 'standalone' measure (21). EQ-5D is designed for self-completion and is cognitively simple, taking only a few minutes to complete. Instructions to respondents are included in the questionnaire. The current 3-level, 5-dimensional format of the EQ-5D will remain unchanged for the immediate future. EQ-5D is one of a handful of measures recommended for use in cost-effectiveness analyses by the Washington Panel on Cost Effectiveness in Health & Medicine (22–24). It has also been used in cancer patients and the minimally important differences has been estimated to be 0.06 for US-index scores (25).

**5.0 Research Design and Methods**

**5.1 Eligibility Criteria**

5.1.1 Histologically documented squamous cell carcinoma or adenocarcinoma of the thoracic esophagus (> 20 cm from the incisors) or gastroesophageal junction are included. Cancers of the cervical esophagus (< 20 cm are excluded).

5.1.2 No distant metastases (M0).

5.1.3 Patients will be stratified by stage (clinical N0 versus clinical N1), and surgeon (RI versus RM versus DF)

5.1.4 Patients with tumours within 3 cm distal spread into gastric cardia as detected by esophagogastroscopy. Tumours that have > 3 cm of spread into cardia of the stomach are considered gastric cancers and are ineligible.

5.1.5 Patients with biopsy (by endoscopic ultrasound, laparoscopy, or laparotomy) proven metastatic supraclavicular nodes are ineligible.

5.1.6 Patients with biopsy proven metastatic celiac nodes are ineligible. Resectable mediastinal nodes are eligible.

5.1.7 No prior chemotherapy for this malignancy.

5.1.8 No prior radiotherapy that would overlap the field(s) treated in this study.

5.1.9 Patients with other malignancies are eligible only if > 5 years without evidence of disease or completely resected or treated non-melanoma skin cancer.

5.1.10 Age > 18 years and able to tolerate tri-modality therapy at the discretion of the treating thoracic surgeon, medical and radiation oncologists. Tumours must be resectable after assessment by the thoracic surgeon.

**5.1.11 Required Laboratory Data:**

Granulocytes > 1.5 x 103 / L

Thrombocytes > 100 x 103 / L

AST, ALT, ALP < 2 times upper limit of normal

Creatinine clearance > 50 ml / min*

x Measurement or calculation based on gender from serum creatinine, age, and body weight (kg) according to the formula below:

For men: (140 - age) x (body weight in kg)

(72 x serum creatinine)

For women: 0.85 x (creatinine clearance)

**5.1.12 Required Diagnostic Procedures**

All patients must undergo esophagogastroduodenoscopy (EGD), CT scan of the chest and upper abdomen, CT scan of the head., Bone scan. or Positron emission tomography is recommended if available.

Bronchoscopy is required for patients with cancers adjacent to the trachea or left main stem bronchus.

Pulmonary function tests (PFTs) that include FEV1, DLCO/VA, and arterial blood gases.

**6.0 Screening and Randomization Phase**

**6.1 Recruitment**

Patients will be recruited from the referrals to either the London Health Sciences Centre or the London Regional Cancer Program. Potential patients may be referred to the study centre by local gastroenterologists, general internists, thoracic surgeons, medical or radiation oncologists or family physicians.

**6.2 Initial Screening**

All potentially eligible patients will be recorded (study logbook) with key demographic data such as name, address, sex, birth date, age, diagnosis and referring physician. A diagnosis of esophageal carcinoma must be established by the referring physician before the patient will be scheduled for an eligibility visit. All patients with potentially resectable esophageal carcinomas will be considered.

**6.3 Eligibility Visit Prior to Randomization**

Potential candidates will be seen by a surgical, medical, and radiation oncologist to be assessed for trial participation.

The following will be obtained at the eligibility visit: (1) written informed consent (2) history of relevant conditions and current medications (3) a physical examination including determination of patient's height, weight, and body surface area (4) baseline laboratory investigations including a PA and lateral chest radiographs; computed tomograms of chest and upper abdomen, computed tomograms of head, bone scan, pulmonary function tests, and arterial blood gases at rest. PET scans are also encouraged if available. Blood work including hemoglobin, total white cell count and differential, platelet count, sodium, potassium, glucose, creatinine, AST, ALP, bilirubin, albumin, LDH, calcium, magnesium. Baseline measures of health utility using the EuroQoL EQ-5D, and measures of quality of life using FACT-E and EORTC QLQ-C25 will be determined. Partial PAR (Patient Assessment Record) will be completed for baseline toxicity.

The eligibility visit will provide an opportunity for referral to other consultants to have medical therapy optimized. Randomization to treatment groups will follow a completed eligibility assessment. All patients eligible to be randomized will be recorded in a study log.

**7.0 Randomization**

With the completion of investigations and staging and the receipt of the baseline data recorded on the Eligibility Visit data collection forms the patient's eligibility will be re-checked and if the patient meets the inclusion and exclusion criteria, the patient will be randomized to one of two treatment groups. Blinded and blocked randomization will be in a 1:1 allocation ratio between treatment arms with stratification by surgeon. Randomization will occur centrally (Thoracic Clinical Trials Office) to ensure concealment of the process. Once randomized, the patient will be followed until death or the end of the study (1 year) and all outcome events will be attributed to the study group to which the patient has been assigned (intent-to-treat-analysis). Follow-up after 1 year will continue as per usual standard clinical practice. No clinical trial tests will be administered.

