**7.1 Overview of Treatment Plan**

The control arm of this study will consist of induction chemotherapy (2 Cycles - Cisplatin plus continuous infusion of 5-Fluorouracil) and concurrent radiation followed by surgical resection of the esophagus. The experimental arm will consist of surgical resection followed by (if required based on final pathological staging) two cycles of chemotherapy (Epirubicin, Cisplatin and continuous infusion of 5-Fluorouracil) and concurrent extended volume radiation treatment with the last 2 cycles. Follow-up of patients with clinic visits of similar frequency to the experimental arm will be required to avoid introduction of bias in recording of time to progression.

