**11.2 Secondary Outcomes**

**11.2.1 Survival at 5 years.** All patients will be followed every 3 months for 2 years and then every 6 months up to 5 years or until death if it occurs before 5 years. Survival will be measured from randomization.

**11.2.2 Disease Free Survival.** Recurrence rates in the two groups including local (gastric or esophageal bed), regional (regional lymph nodes), and distant recurrences (supraclavicular lymph node, liver, peritoneal carcinomatosis, or lung, brain, etc.) will be compared. Disease free survival will be measured as the time from patient entry onto study until the first malignant disease recurrence.

**11.2.3 Site of Treatment Failure.** The location of the first site of malignant disease recurrence will be recorded. Local failure occurs within the gastric or esophageal bed, or regional lymph nodes. Distant failure occurs in the supraclavicular lymph nodes, liver, peritoneal carcinomatosis, pleura, lung, bones, brain, or elsewhere not considered local.

**11.2.4 Toxicities**. Possible adverse drug or radiation events will be reported as described in the London Regional Cancer Program Patient Assessment Record (PAR).

**11.2.5 Completeness of Resection.** The number of R0, R1, R2, and unresectable patients will be compared.

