**11.2.6 Economic Evaluation.** Within the clinical trial we will also conduct an economic comparison of the two treatments. In summary, the viewpoint of the economic study will be that of a Provincial Ministry of Health and we will therefore document all direct health care costs associated with the treatment strategies over the 5-year period of follow-up. Case report forms will be designed to document physical items of resources consumed (i.e., tests, procedures, hospital stay) and unit prices will be estimated for resources using cost-accounting methods. In a circumstance where one of the tri-modality therapies is both more costly and more effective (i.e., greater number of QALYs) we will calculate the incremental cost per QALYs as the ratio of the difference (treatment minus control) in cost to the difference in QALYs. Incremental cost per QALYs estimates will be presented with associated 95% confidence intervals estimated by a resampling technique known as bootstrapping. To further explore uncertainties in the data and analysis we will also conduct extensive sensitivity analyses. We will attempt to project, using available data, costs, and outcomes to 5 years to ascertain whether the economic appraisal is sensitive to the time horizon of analysis.

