**12.1 Follow-up Schedule**

The follow-up visits will occur at the discretion of the treating surgical, medical, and radiation oncologists. All patients will be followed for events until 60 months or death. Routine care will include a history and physical and a chest radiograph. Quality-of-Life, toxicities and morbidity data will be completed only during the first year following randomization at baseline, and every 2 months up to 1 year.

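### Sections 7.0, 11.2.1 and 12.1 give three incompatible follow-up rules, which exposes disease-free survival and site of first failure, and costs are collected for 5 years against 1 year of EQ-5D

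*Protocol*

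**What the plan says.** **Duration and visits.** Three sections of the protocol govern follow-up.

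- Section 7.0 (Randomization): "the patient will be followed until death or the end of the study (1 year"). It continues: "Follow-up after 1 year will continue as per usual standard clinical practice", and "No clinical trial tests will be administered".
- Section 11.2.1, on five-year survival, sets this schedule: "All patients will be followed every 3 months for 2 years and then every 6 months up to 5 years". Follow-up stops sooner for a patient who dies, and survival is counted from randomization.
- Section 12.1 (Follow-up Schedule): "The follow-up visits will occur at the discretion of the treating surgical, medical, and radiation oncologists". The same section then commits to following every patient for events until 60 months or death.

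**Visit frequency by arm.** Section 7.1 says that clinic visits at a frequency similar to the experimental arm "will be required to avoid introduction of bias in recording of time to progression".

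**Economic data.** Section 11.2.6 will "document all direct health care costs associated with the treatment strategies over the 5-year period of follow-up" and report an incremental cost per QALY. It also says that costs and outcomes will be projected to 5 years to test sensitivity to the time horizon. Section 12.1 says that quality-of-life, toxicity and morbidity data "will be completed only during the first year following randomization", at baseline and every 2 months.

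**The concern.** A site could end scheduled follow-up at 1 year, run a fixed schedule to 5 years, or see patients whenever the clinician chooses, and in each case point to a section that allows it.

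This matters most for disease-free survival (11.2.2) and site of first failure (11.2.3). Recurrence is dated when someone looks for it, so both outcomes inherit the visit pattern. Treatment is not blinded (17.2), and the arms differ in when patients attend for treatment. Section 7.1 shows that the authors saw this risk, but the discretion in 12.1 and the usual-practice rule in 7.0 do not secure the safeguard. An analysis plan cannot repair this afterwards, because it cannot create visits that did not take place.

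The economic evaluation has a related problem. A cost-per-QALY ratio needs costs and utilities over the same period, and the protocol collects them over different ones.

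**Working it through.** The protocol has no calculation of its own for follow-up. Its one sample size, for FACT-E at 1 year, is not touched by this point and reproduces: 2 × 25² × (1.960 + 0.842)² / 15² = 43.6, rounded up to 44 per arm.

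**Step 1. The three rules side by side**

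| Section | End of follow-up | Visit timing after year 1 |
|---|---|---|
| 7.0 | 1 year, called the end of the study | Usual practice, no trial tests |
| 11.2.1 | 5 years or death | 3-monthly to 2 years, then 6-monthly |
| 12.1 | 60 months or death, for events | Clinician's choice |

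The 11.2.1 schedule contains 24/3 + 36/6 = 8 + 6 = 14 visits. Of these, 12/3 = 4 fall in year 1, so 10 of 14 lie beyond the point at which 7.0 hands patients to usual practice. Sections 11.2.1 and 12.1 agree on duration but not on visit timing. Section 7.0 agrees with neither on duration.

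**Step 2. What a literal 1-year stop would lose**

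Inputs: the median overall survivals of 14.1 and 47.5 months from the investigators' own earlier series (1.0 Introduction). Assumption: exponential survival, so the proportion dead by month t is F(t) = 1 − exp(−t × ln 2 / median).

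| Median (months) | F(12) | F(60) | Seen by year 1, F(12)/F(60) | Missed |
|---|---|---|---|---|
| 14.1 | 0.446 | 0.948 | 0.47 | 53% |
| 47.5 | 0.161 | 0.583 | 0.28 | 72% |

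In an arm of 48 this is 21.4 of 45.5 expected deaths at the shorter median and 7.7 of 28.0 at the longer.

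The exponential shape is only approximate. The same series reports 5-year survival of 0% and 48%, that is 100% and 52% dead, against 95% and 58% here.

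**Step 3. Which outcomes depend on visit timing**

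- FACT-E over 1 year: its own 2-monthly schedule lies wholly within year 1. Unaffected.
- Overall survival: the date of death hardly depends on visits. Section 12.1 keeps events to 60 months, and 12.2 requires a form and detailed information for every death. Little affected if those commitments are kept.
- Disease-free survival and site of first failure: both are dated or classified at detection. Exposed.

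The size of any bias between arms would need the difference in visit intervals between arms. The protocol states none, so none is computed.

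**Step 4. Costs against utilities**

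Section 4.0 counts a utility instrument among the quality-of-life measures, and 4.3 describes EQ-5D, so the first-year limit in 12.1 covers it. Costs span 5 years and EQ-5D 1 year, so 5 − 1 = 4 years of cost have no observed utility beside them. Section 11.2.6 also plans both to document costs over 5 years and to project them to 5 years, without saying which horizon is the base case.

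**The case against.** The strongest reply is that the sections can be read together: trial tests and questionnaires end at 1 year, while events are followed to 60 months. The collection of details on every death (12.2) supports this. It largely protects overall survival, and a reader who infers that 5-year survival cannot be obtained goes further than the text allows. It does not remove the conflict. Section 7.0 calls 1 year the end of the study and substitutes usual practice for scheduled visits, and even on the generous reading 11.2.1 and 12.1 still disagree on visit timing.

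A reader might also infer that recurrence will be found earlier in the experimental arm because of its postoperative chemotherapy visits. The documents do not show this. Control patients attend for 28 radiation fractions, resected pT1-2N0 patients in the experimental arm are generally not offered adjuvant therapy, both arms have 2-monthly data collection in year 1, and 7.1 asks for similar frequency. The 3- and 6-month intervals in 11.2.1 are successive phases for all patients, not a contrast between arms. What stands is that 12.1 removes the assurance of equal assessment.

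On the economic side, 11.2.6 already foresees projection to 5 years and does not fix 5 years as the horizon of the ratio. A modelled 5-year result is therefore legitimate. The mismatch in observed data remains, as does the missing base-case horizon.

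Finally, the trial is not powered for secondary outcomes (17.2), which limits the consequence but does not excuse the contradiction.

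**Conclusion.** The concern holds as an internal contradiction that affects secondary outcomes. Sections 7.0, 11.2.1 and 12.1 cannot all be followed, and discretionary visits undercut 7.1. Disease-free survival and site of first failure are exposed, overall survival only slightly provided the 60-month commitment is honoured, and the primary FACT-E outcome not at all.

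A literal 1-year stop would miss about 53% to 72% of 5-year deaths. That range rests on exponential survival and on two medians from an earlier node-positive series, and it applies only if 7.0 overrides the other sections. The direction and size of any detection bias between arms cannot be stated.

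QALYs after year 1 can only be modelled. This does not make a 5-year cost per QALY impossible, but such a result should not be presented as observed.

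**What to change.** 1. **Section 7.0:** state that 1 year ends the primary quality-of-life period and the trial tests, and is not the end of follow-up for survival and recurrence.
2. **Section 12.1:** for outcome assessment, replace the discretion sentence with the 11.2.1 visit times, counted from randomization and identical in both arms. Additional clinical visits stay free. This also gives effect to 7.1.
3. **Section 11.2.6:** make the base-case cost per QALY a 1-year horizon, where costs and EQ-5D both exist, and label 5-year results as modelled.

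The cost is protocol wording. No visits are added beyond those already promised in 11.2.1. The small downside is that clinicians lose some freedom in timing outcome visits. Collecting EQ-5D after year 1 is not part of this fix: it would be new data collection and would go against the current limits in 7.0 and 12.1.
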